**Fig. 2 Fig2:**
[figure not shown]
Hypothesized causal pathway of the effect of the intervention and its outcome measures

Furthermore, the intervention benefits are hypothesized to spill over to the entire community. Following a socio-ecological framework [45, 46], the child’s immediate environment affected by the intervention would be the microsystem (the family) and the mesosystem (for example, parent-teacher meetings, the neighborhood, and social gatherings at the village level). At both these levels, one could expect counseled mothers of anemic children to modify the behaviors of mothers of non-anemic children, with respect to IFA consumption and dietary iron intake, thereby reducing the overall prevalence of anemia at the cluster level. Thus, the intervention is evidence based, contextually relevant, uses locally relevant resources, and has the potential to influence national policy.

#### Lay health worker training

LHWs in the intervention villages [*n* = 30] will receive training under four separate hands-on workshops over a period of 6 months. Training will occur with the use of role play, facilitation, and flip charts to help develop counseling and education skills of the LHWs. Training will take place at a location different from the LHWs’ habitual training/supervision sites, to minimize the risk of contamination. LHWs will be trained to deliver five monthly education and counseling sessions to mothers/caregivers of anemic children. Specifically, these sessions will aim to improve mothers’ knowledge regarding anemia and its consequences, the treatment of iron deficiency anemia with IFA, the importance of adherence to IFA treatments, sources of iron-rich food, diet modification behaviors, and hygiene. The possibility of contamination during LHW-supervisor monthly meetings, due to interaction between control group and intervention group LHWs, is minimal. LHWs in the control group neither receive training nor have access to training and intervention materials and will therefore be unable to replicate the intervention in their villages.

### Components of the Intervention

i)*Enrollment and screening for anemia*All eligible participants providing informed consent will be enrolled in the trial, provide information for a baseline questionnaire, have anthropometric measurements, and venous blood obtained by phlebotomy to screen for anemia by the research team.ii)*Iron supplementation*A core preventive measure common to both trial arms is the delivery of iron supplements. All enrolled non-anemic participants are eligible for IFA supplements (tablets containing 20 mg elemental iron, 8 tablets/month) in line with National Iron + guidelines [25]. The guidelines recommend 20 mg IFA dispensed as syrup biweekly throughout the period 6–60 months and deworming for children 12 months and older. Since IFA syrup was not available in Karnataka, for the purpose of this trial, IFA is provided as 20 mg tablets. All enrolled participants detected with anemia (Hb ≥ 8 and ≤ 11 gm/dL) [40] in both arms of the trial are eligible for the therapeutic IFA dosage to control iron deficiency anemia (tablets containing 20 mg elemental iron, 20 tablets/month for 5 months). All subjects with acute infections or fever will be excluded during enrollment to the trial. Furthermore, during dispensation of IFA tablets, LHWs will advise mothers to withhold these during periods of fever or acute infections.iii)*Education and counseling*Only mothers/caregivers of anemic children (Hb ≥ 8 and ≤ 11 gm/dL) in the intervention arm will receive five monthly education and counseling sessions delivered by the LHW over the 6-month intervention period (Fig. 1).iv)*Monitoring of adherence to IFA*From the second counseling visit onward, LHWs in the intervention arm perform monthly pill counts to assess adherence to IFA dispensed only to mothers/caregivers of anemic children in the previous month and document the side effects of IFA, if any. In accordance with precautions in the guidelines, LHWs will advise mothers to withhold supplemental and treatment IFA during periods of fever or acute infections. A similar monthly assessment of adherence for mothers of anemic children in the control arm will not be performed. However, at the end of the 6 months of intervention, an assessment adherence to IFA in the previous 30 days will be performed for all participants in both arms of the trial.

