### Outcomes

The primary outcome will be the difference in anemia cure rate between the experimental arms at the end of 6 months from the intervention’s start, in children found to be anemic at baseline. In addition, we will assess several secondary outcomes occurring along the hypothesized causal pathway of the intervention effect (Fig. 2), including: 1) difference in changes of knowledge and practice of mothers of anemic children from baseline to follow-up, 2) differences in the estimated 24-hour dietary iron intake among anemic participants exposed and not exposed to the intervention, 3) difference in net improvements in individual hemoglobin values between baseline and 6 month follow-up among anemic children exposed and not exposed to the intervention, 4) net improvements in mean ferritin values among anemic participants exposed and not exposed to the intervention, and, 5) difference in the cluster level anemia prevalence between experimental arms. Additional process indicator data include evaluation of the proportion of expected IFA doses delivered to children in the study (adherence to iron treatment), maintenance of LHW records of delivery of the intervention and IFA, and recording of the incidence of side effects of IFA supplements in children. Qualitative research on the acceptability, perceptions, and experiences of the LHWs regarding the training for and the actual delivery of the intervention will be conducted using focus group discussions. These data will help identify key assumptions and limitations of underlying intervention feasibility and sustainability and scaling-up, particularly when involving LHWs at the national level.

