### Protocol of data collection

At study entry, a baseline questionnaire will record participant information. An additional file shows this in more detail [see Additional file 1]. Participants will also have a baseline sample of anticoagulated venous blood obtained to detect anemia and measure serum ferritin. All recruited participants will have a hemoglobin value estimated using an automated cell counter (Sysmex 405, Transasia laboratory systems, Japan). Within a few days the research team will provide mothers/caregivers with results of the hemoglobin values and anthropometry, and cluster LHWs with a list of anemic and non-anemic children. The list will permit LHWs in each cluster to organize the delivery of dose appropriate IFA to anemic and non-anemic children and to identify mothers of anemic children for delivery of monthly education and counseling.

The date of delivery of the first month’s supply of IFA to the mothers of children in a cluster will herald the start of the intervention in that cluster. LHWs will deliver IFA to mothers of non-anemic children at the ADC during routine monthly visits. LHWs will typically deliver IFA together with education and counseling to mothers of anemic children at their homes. From the second visit onward, adherence data will be collected by the LHW, and the remaining IFA pills/empty strip will be obtained from the mother. In the control arm, LHWs will deliver IFA as usual in the setting of the ADC and will not deliver education and counseling to mothers of anemic children or collect monthly IFA adherence data. Approximately 6 months from the day of delivery of the first IFA supplement, the research team will perform a follow-up visit to collect 24-hour dietary recall data, anthropometry, and information on adherence to IFA in the previous month from all enrolled participants. During this time, a repeat phlebotomy to estimate hemoglobin is performed for all participants in the cluster, and the trial is completed.

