#### Monitoring of side effects and trial supervision

Details regarding side effects to IFA supplements will be collected by the LHW and notified to the research team. In the event of side effects that are deemed related to IFA (either by the LHW or the research team), participants are advised by the LHW to discontinue IFA and report to the primary health center for evaluation. Since the intervention under comparison is non-invasive, the IFA supplements in the protocol follow national recommendations, and the setting is not a malaria endemic region, the occurrence of serious adverse events (SAEs) is unlikely. An interim analysis of the trial will take place when all subjects have been recruited and all 30 clusters have completed 3 months of delivery of the intervention. This analysis will be conducted in a blinded manner by an independent data safety and monitoring board (DSMB) consisting of experts in clinical medicine, epidemiology, and statistics. The primary aim of the interim analysis is to assess if the intervention arm shows a clearly better, or worse, outcome than the control arm as well as to evaluate SAEs.

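### The only scheduled side-effect enquiry described is in the intervention arm, so the recorded side-effect incidence cannot be compared between arms

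*Protocol article*

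**What the plan says.** All places are in the Protocol article.

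- **Components of the Intervention, item iv.** "From the second counseling visit onward, LHWs in the intervention arm perform monthly pill counts to assess adherence to IFA". The same sentence has them do this for "mothers/caregivers of anemic children in the previous month and document the side effects of IFA, if any". With five monthly sessions, that is up to four occasions (sessions 2 to 5), for anemic children only.
- **Same item, control arm.** "A similar monthly assessment of adherence for mothers of anemic children in the control arm will not be performed". Protocol of data collection repeats this: control LHWs hand out iron and folic acid (IFA) at the day care center and "will not deliver education and counseling to mothers of anemic children or collect monthly IFA adherence data".
- **Lay health worker training.** "LHWs in the control group neither receive training nor have access to training and intervention materials".
- **6-month visit, both arms (Protocol of data collection).** The research team will "collect 24-hour dietary recall data, anthropometry, and information on adherence to IFA in the previous month from all enrolled participants", and repeats the blood draw. Side effects are not listed.
- **Outcomes.** The process indicators include "recording of the incidence of side effects of IFA supplements in children".
- **Monitoring of side effects and trial supervision.** The general statement reads: "Details regarding side effects to IFA supplements will be collected by the LHW and notified to the research team". No arm, schedule or form is given. The data safety and monitoring board (DSMB) looks at whether the intervention arm does clearly better or worse, and evaluates serious adverse events, once clusters have completed 3 months of delivery.

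**The concern.** Anemic children in both arms are eligible for the same iron regimen, so side-effect incidence is a quantity a reader would naturally set side by side. As described, the two arms are observed with different intensity. One is asked monthly, typically at home, by a trained worker who is already checking the tablets. The other has no scheduled question. Non-anemic children, who also receive iron, have no scheduled question in either arm.

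Two things are at stake. First, an excess can appear in the intervention arm with no true difference behind it. Second, the intervention is meant to raise adherence, which could truly increase side effects. With unequal collection, that effect could not be told apart from better detection. The primary and secondary outcomes are untouched.

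**Working it through.** **1. Which enquiry exists for whom, as described**

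| Group | Monthly scheduled enquiry | General LHW notification | Side-effect item listed at 6 months |
|---|---|---|---|
| Intervention, anemic | Yes, from session 2 | Yes | No |
| Control, anemic | None described | Yes, no schedule | No |
| Non-anemic, both arms | None described | Yes, no schedule | No |

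Adherence is also checked monthly in one arm only, but item iv adds an end-of-study adherence assessment for everyone. No such common assessment is described for side effects.

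**2. The plan's own numbers**

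The article states no side-effect rate, so only its sample size can be reproduced.
- Cure rates of 30% and 42%, two-sided 0.05, 80% power, no continuity correction: 250 per arm, 500 in total, as stated.
- Design effect: 1 + (25 - 1) × 0.05 = 2.2, and 500 × 2.2 = 1,100, as stated.
- 10% loss: 1,100 / 0.9 = 1,222, against the stated 1,220 (610 per arm), a rounding difference.

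For the illustration I use 1,100 / 2 = 550 anemic children per arm after loss. The effective number is 550 / 2.2 = 250 per arm.

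**3. Illustration of the artefact**

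Observed incidence = true incidence × share detected. With equal true incidence, the observed ratio is the ratio of the two shares, whatever the true incidence. The shares are assumptions: 80% or 90% with monthly asking, and 30%, 50% or 70% without. The last column is the chance of a significant excess in the intervention arm if someone ran a two-proportion test (two-sided 0.05) with 250 effective children per arm. The formula is Φ[(p₁ - p₂ - 1.96·√(2p̄(1-p̄)/250)) / √((p₁(1-p₁) + p₂(1-p₂))/250)], where p̄ is the mean of p₁ and p₂. True incidence is assumed to be 10%.

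| Detected, intervention vs control | Observed | Spurious ratio | Chance of false excess |
|---|---|---|---|
| 90% vs 30% | 9% vs 3% | 3.00 | 0.81 |
| 90% vs 50% | 9% vs 5% | 1.80 | 0.42 |
| 90% vs 70% | 9% vs 7% | 1.29 | 0.13 |
| 80% vs 30% | 8% vs 3% | 2.67 | 0.69 |
| 80% vs 50% | 8% vs 5% | 1.60 | 0.27 |
| 80% vs 70% | 8% vs 7% | 1.14 | 0.06 |

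At a true incidence of 5% to 20%, the last column runs from 0.05 (80% vs 70% at 5%) to 0.99 (90% vs 30% at 20%). With equal shares the ratio is 1.00, and the chance of a false excess in that direction is the nominal 0.025.

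**The case against.** **No comparison is planned.** Side-effect incidence is a process indicator, and no test by arm is stated. The DSMB task names outcome and serious adverse events. A reader might infer that a false safety signal will reach the DSMB. The article does not support that: it does not say the DSMB will compare non-serious side effects, and serious events depend much less on monthly asking. This stands and limits the harm.

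**Control-arm collection is not ruled out.** The monitoring section has no arm limit, control LHWs do meet mothers when handing out IFA, and the stated exclusions name adherence and counseling, not side effects. A reader might infer that control reports rest wholly on mothers volunteering complaints. The article does not say so. It does not describe any matching enquiry either.

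**Control LHWs may be trained.** The Discussion says LHWs in both arms receive training, against the section on LHW training. The two need reconciling, but neither mentions side-effect collection in the control arm.

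**The 6-month list is incomplete.** It also omits the mothers' knowledge questionnaire and follow-up ferritin, which are planned elsewhere, so absence from it is weak evidence in a condensed article. This is fair. The point rests mainly on the arm-specific procedure that is stated, not on that omission.

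**The size is assumed.** Correct. Side effects recorded by one LHW per village may also cluster more than an ICC of 0.05 implies, which would lower the chances shown above. The ratios would not change.

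**Conclusion.** The point holds in a limited form. Followed as written, the plan yields a side-effect incidence collected with different intensity by arm. The expected direction is more recorded events in the intervention arm, even with equal true incidence. It is too strong to say that an excess will appear: this is an expectation, and its size cannot be derived from the documents. With detection of 80-90% against 30-70%, the spurious ratio is 80/70 = 1.14 to 90/30 = 3.0. At the mild end a false signal is unlikely; at the other end it is likely.

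The harm is confined to the incidence listed under Outcomes and to any comparison by arm drawn from it. It is worth correcting because the correction is cheap and the information cannot be recovered afterwards.

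**What to change.** 1. Reconcile Components of the Intervention, Outcomes, Protocol of data collection, and Monitoring of side effects, so that they say who is asked about side effects, when, and in which arm.
2. At the existing 6-month research-team visit, ask all participants in both arms, anemic and non-anemic, the same side-effect and serious-event questions with the same short recall window. Base any between-arm side-effect comparison on these answers only. The 30 days already used for adherence is one option. Check first that the window overlaps with dosing: the therapeutic supply is described as 5 months and the visit falls at about 6, so the last 30 days might cover little tablet intake.
3. Report the LHWs' monthly side-effect records as a description of the intervention arm.
4. The 6-month answers come too late for the 3-month interim look. For that look, continue to pass all LHW-notified serious adverse events from both arms to the DSMB, and tell it that LHW-recorded non-serious side effects are not comparable by arm.

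The cost is a few questions at a visit already made and a sentence or two of protocol text. A short window misses earlier events. Recall may also still differ by arm, because intervention mothers will have been counseled and asked monthly, so most but not all of the asymmetry is removed.

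### For children anemic at baseline, the only adherence assessment made in both arms covers the month after their five-month iron supply nominally ends, and side effects may be ascertained unequally by arm

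*Protocol article*

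**What the plan says.** All locations are in the protocol article.

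- **Supply.** *Components of the Intervention*, item ii, gives anemic children in both arms "tablets containing 20 mg elemental iron, 20 tablets/month for 5 months". Non-anemic children get 8 tablets a month with no stated end.
- **Clock.** *Protocol of data collection* starts the intervention in each village on the day the first month's supply is delivered. The end visit is set as follows: "Approximately 6 months from the day of delivery of the first IFA supplement, the research team will perform a follow-up visit".
- **Adherence, both arms.** Item iv plans one assessment at the end of the 6 months: "an assessment adherence to IFA in the previous 30 days will be performed for all participants in both arms of the trial". *Protocol of data collection* repeats it as "information on adherence to IFA in the previous month from all enrolled participants".
- **Adherence, intervention arm only.** Item iv says that from the second counseling visit the lay health workers (LHWs) count pills: "LHWs in the intervention arm perform monthly pill counts to assess adherence to IFA dispensed only to mothers/caregivers of anemic children". The same sentence has them document side effects. Item iv then states that no similar monthly adherence assessment is made in the control arm.
- **Side effects in general.** *Monitoring of side effects and trial supervision* says: "Details regarding side effects to IFA supplements will be collected by the LHW and notified to the research team". It names neither an arm nor a schedule. *Outcomes* lists side-effect incidence among the process data.
- **Process indicator.** *Outcomes* also lists an indicator labelled adherence, but defines it by the share of planned doses that were delivered.

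**The concern.** The intervention is meant to work largely through better adherence. The *Background* hypothesis and the *Rationale for the intervention and its development* both say so, and the *Discussion* holds that studies should show how an intervention works as well as whether it does. That calls for a measure of tablets taken during treatment that means the same thing in both arms.

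For anemic children the common measure appears to look at the wrong month. If it does, a null result on cure could not be traced to unchanged adherence or to improved adherence without effect, and a positive result could not be credited to the proposed pathway. This is data collection fixed in the protocol, so no later analysis plan could recover intake that was never recorded in the control arm.

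Side effects raise a related worry. If one arm is asked every month and the other has no stated schedule, a difference in incidence may reflect how often the question was put.

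**Working it through.** The plan gives no figure of its own for this point, so the check is date arithmetic on its stated schedule.

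**Inputs.** Five monthly supplies of 20 tablets (20 × 5 = 100), the first on day 0; visit at about 6 months; recall window of 30 days. My assumption: a month is 30.4 days.

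**Nominal schedule.**
- Deliveries at months 0 to 4: days 0, 30, 61, 91 and 122.
- End of supply: 5 × 30.4 = day 152. If the last 20 tablets are taken one a day: 121.6 + 20 = about day 142.
- Visit: 6 × 30.4 = day 182.4. Window: 182.4 − 30 = day 152.4, to day 182.4.
- Overlap = max(0, min(supply end, visit) − max(visit − 30, last delivery)) = max(0, 152.0 − 152.4) = **0 days**.

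**Slippage.** The visit is only approximately at 6 months and no delivery dates are fixed, so I varied both. These values are assumptions. The lower overlap has the last 20 tablets taken daily; the higher has them spread over the month.

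| Last delivery | Visit | Overlap with last supply (days) |
|---|---|---|
| on time | 6 months | 0 |
| on time | 6.5 months | 0 |
| on time | 5.5 months | 4.4 to 14.8 |
| 7 days late | 6 months | 0 to 6.6 |
| 14 days late | 6 months | 3.2 to 13.6 |
| 30 days late | 6 months | 19.2 to 29.6 |

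One line in full, for 14 days late: last delivery 121.6 + 14 = 135.6; supply ends at 155.6 or 166.0; minus 152.4 gives 3.2 or 13.6 days.

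The window thus catches the last supply only when something moves off the stated schedule. Leftover tablets are the other route, and they partly reflect doses missed earlier. *Protocol of data collection* also has remaining tablets or empty strips obtained from mothers at the intervention arm's monthly visits, with no such step described for controls. Leftovers at month 5 may therefore differ by arm for reasons unrelated to intake in that month.

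**Can another source stand in?**
- Pill counts: intervention arm only, so they allow no comparison.
- The indicator in *Outcomes*: not limited to one arm, but it measures delivery, not intake.

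**Side effects.** Side by side, item iv ties monthly documentation to intervention-arm visits for anemic children, while the monitoring section has LHWs collect side effects with no arm and no timetable. Control-arm reports are possible, but no equal frequency of asking is laid down.

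**The case against.** Adherence is neither the primary nor a listed secondary outcome; it is a process indicator, and *Statistical analysis* plans no adherence comparison. Pill counting is listed as an intervention component, and the *Discussion* treats monitoring of compliance as part of what is tested, so its absence from the control arm is deliberate. The follow-up form is not shown and may hold more detail. All of this stands, and it limits the weight of the point. It does not change the window, which two sections state in the same way.

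A reader might infer more than the documents support:

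- *That none of the 100 treatment tablets can fall in the window.* This is true only nominally. The visit time is approximate, the five sessions are spread across a six-month period, and mothers are told to withhold tablets during fever or infection, so a child who follows instructions may have some left.
- *That the measure fails for everyone.* The timing problem concerns anemic children. The supplement for non-anemic children has no stated end, so the window may fit them.
- *That the measure will reverse the comparison.* Leftovers make this possible; nothing shows that it will happen.
- *That the fifth supply is never counted.* Counts run from the second visit onward, and the handling of the last supply is not stated.
- *That control families have no monthly contact, or that no side effects are collected there.* The abstract has control LHWs distribute tablets as in the intervention arm, where distribution is monthly, and the side-effect monitoring section names no arm. Only equal, scheduled inquiry is lacking.

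**Conclusion.** The point holds for children anemic at baseline. On the stated schedule, the only intake measure common to both arms begins when the five-month supply ends, with a nominal overlap of 0 days. It rises to between 3 and 15 days under modest assumed slippage (a visit half a month early, or a last delivery 14 days late), and approaches the full window only if the last delivery is about a month late. Because overlap depends on delay or leftovers, it is not a valid basis for comparing the arms on intake during treatment, and no other planned source supplies one.

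Side-effect incidence may be ascertained unequally and may look higher in the intervention arm. The documents do not support saying that it will, or by how much.

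The hemoglobin-based primary outcome is not affected. What is weakened is the trial's ability to test its stated mechanism. The conclusion rests on deliveries at roughly monthly intervals from day 0 and a visit close to month 6.

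**What to change.** At the 6-month visit, have the research team put the same items to both arms. For anemic children, tie them to the last treatment supply dispensed: tablets received, taken and left over. Add one side-effect question, worded identically and covering the same period in both arms. Base any between-arm comparison of adherence or side effects on these items, and use LHW pill counts and LHW side-effect records only to describe delivery of the intervention. Notification of side effects to the research team continues as planned.

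Reconcile the text on supply duration (*Components of the Intervention*, item ii) with the text on the adherence window (item iv and *Protocol of data collection*). No change to the supplement schedule is implied.

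The cost is a few questions at a visit already planned. Recall reaches back one to two months (182 − 152 = 30 days to 182 − 122 = 60 days), and counseled mothers may be more inclined to give the desired answer. Asking about all five supplies would lengthen recall to as much as six months and enlarge that error, so the last supply is the better anchor.
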